## Abstract

**Background:**

Most people with dementia live in the community, not in residential care. Therefore, quality informal care for them is critical for managing behavioural and psychological symptoms of dementia (BPSD). Music therapy has been shown to reduce BPSD. However, no randomised controlled trial has examined the effects of music interventions delivered by caregivers in home settings. The HOME-based caregiver-delivered music intervention for people living with dementia (HOMESIDE) trial aims to evaluate the effectiveness of a 12-week music intervention in addition to standard care for BPSD. This article describes the statistical analysis plan.

**Methods and analysis:**

HOMESIDE is a large, pragmatic international three-arm parallel-group randomised controlled trial. Dyads (persons with dementia and caregiver) in Australia, Germany, the UK, Poland and Norway were randomised to receive music and standard care, reading and standard care or standard care alone. The primary outcome is BPSD (proxy) of the person living with dementia, measured using the Neuropsychiatric Inventory-Questionnaire (NPI-Q) at 90 and 180 days post-randomisation. Longitudinal analysis will compare NPI-Q severity between music and standard care versus standard care alone. Secondary outcomes include quality of life and depression (both person with dementia and caregiver), cognition (person with dementia only), distress, resilience, competence and caregiver-patient relationship (caregiver only). Treatment effects will be obtained at 90 and 180 days post-randomisation, where applicable. Safety outcomes (adverse events, hospitalisations, deaths) will be summarised.

**Discussion:**

This statistical analysis plan provides a detailed methodology for the analysis of HOMESIDE and will improve the validity of the study and reduce the potential for bias.

**Trial registration:**

Australian New Zealand Clinical Trials Registry ACTRN12618001799246. Registered on November 05, 2018. ClinicalTrials.gov NCT03907748. Registered on April 09, 2019.

## Introduction

The majority of people with dementia live in the community and not in residential care settings [1]. Therefore, personalised care from a family caregiver (CG) is often needed for a person living with dementia (PwD). This personalised care offers benefits to the PwD by enabling them to remain in an environment familiar to them. However, research has shown that managing the behavioural and psychological symptoms of dementia (BPSD) can be difficult for CGs, leading to poor physical and mental health of CGs [2, 3]. This poor health in a CG has the potential to lead to poorer health and well-being for the PwD. Therefore, there is a need to support CGs in providing care.

Music therapy offers the potential to provide CGs with support in managing PwD. This therapy is a registered psychosocial National Health Service intervention in the United Kingdom (UK) to address the needs of people living with dementia [4]. Existing cognitive-behavioural or psychoeducational approaches designed to support CGs have suffered from poor adherence as CGs were unable to attend the scheduled appointments for the intervention [5, 6]. Home-based programmes may be preferable due to their convenience for CGs.

The HOME-based caregiver-delivered music intervention for people living with dementia (HOMESIDE) study is designed to examine the effectiveness of a music intervention (MI) in addition to standard care (SC) delivered directly by CGs in a home setting following training in the intervention delivery by music therapists. The aim of the HOMESIDE randomised controlled trial (RCT) is to demonstrate the effectiveness of the 12-week MI plus SC on the short-term BPSD at the end of the intervention of PwD living at home and being cared for by a cohabitating CG compared with SC (primary) and to evaluate the effectiveness of MI plus SC, compared with a reading intervention (RI) plus SC (secondary). The RI plus SC condition was chosen as an active control group as some evidence suggests reading to and with PwD can have a positive impact on BPSD [7, 8]. The primary BPSD outcome of the trial is the total severity score as measured by the Neuropsychiatric Inventory–Questionnaire (NPI-Q) at 90 days post-randomisation for the PwD. The protocol for the HOMESIDE trial which includes full details of the intervention groups has been published [9].

This paper describes the planned statistical analysis for the HOMESIDE trial and supersedes the plan provided in the trial registries and published protocol. Any changes to the statistical analysis plan between publishing and unmasking will be tracked. The final statistical analysis plan will be approved during the masked data review and signed before breaking the treatment allocation code, after which any changes will be considered post hoc.

## Methods and design

### Setting

HOMESIDE originally planned to recruit participants from six sites in five countries: Australia (Queensland and Victoria), Germany, Norway, Poland and the UK. Initially, training between music therapists and CGs, as well as outcome assessments for all participants, was planned to take place in person. Therefore, participants in Australia were originally only going to be recruited from the states of Queensland and Victoria due to the geographical size of the country. To facilitate the in-person delivery of the intervention across geographically diverse regions, randomisation within Australia was stratified to these two states. Due to the outbreak of coronavirus disease (COVID-19) in March 2020, for the safety of participants and the HOMESIDE team, the delivery of all clinical trial activities moved to an online format (via secured video conference software). This provided scope to recruit participants beyond Queensland and Victoria in Australia. Therefore, the Queensland stratum was subsequently redefined as ‘Northern Australia’ to capture participants recruited from New South Wales, Queensland or the Australian Capital Territory. The Victoria stratum was subsequently redefined as ‘Southern Australia’ and covered participants recruited from the rest of Australia (i.e. Victoria, South Australia, Tasmania, Western Australia, Northern Territory).

### Design

HOMESIDE is a large international pragmatic, three-arm parallel-group RCT. Dyads consisting of the PwD and cohabitating CG were randomised to one of the three arms: MI plus SC, RI plus SC or SC alone. HOMESIDE is a superiority trial, with the hypothesis that MI plus SC is superior to SC alone (primary) and RI plus SC (secondary) in relation to BPSD at 90 days post-randomisation. Online assessments occurred at each MI/RI instruction session and follow-up at 90 and 180 days post-randomisation (Fig. 1). The study was prospectively registered at the Australian New Zealand Clinical Trials Registry (ACTRN12618001799246, registered on 05 November 2018) and ClinicalTrials.gov (NCT03907748, registered on 09 April 2019).

**Fig. 1 Fig1:**
[figure not shown]
HOMESIDE illustration of study design

### Intervention groups

The interventions were described fully in the detailed published protocol [9]. In brief, the MI involved a 2-h home-based training session in which a qualified music therapist instructed the CG on methods and strategies for using music to assist with care and connection with the PwD. This training covered activities such as singing or listening to familiar or preferred songs and engaging in dialogues about these with the PwD, movement to music and playing instruments. The RI involved a 2-h home-based RI instruction session delivered by a qualified practitioner to engage the PwD during and following the RI. The training covered the CG reading aloud to the PwD, the PwD reading aloud to the CG, listening to audiobooks, playing word games and discussion of the text. Following training, CGs were instructed to deliver the MI or RI at least five times per week for 30 min over a 12-week period. CGs allocated to SC alone were instructed to care for the PwD in their usual manner.

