### Sample size

The trial was designed to recruit a total of 495 dyads (165 per arm) to detect a difference of 3 points in NPI-Q total severity score between the MI plus SC and SC alone at 90 days post-randomisation. This assumes 90% power, a two-tailed significance level of 5%, an equal standard deviation of 7.5 points in the groups, no correlation between baseline and 12 weeks (conservative) and 20% attrition. A 3-point change from baseline in NPI-Q total severity score is considered a clinically meaningful difference [11]. No interim analyses to stop the trial early were planned, and no interim analysis was conducted.

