### Primary outcome

The estimate corresponding to the primary estimand of the NPI-Q severity of the PwD at 90 days will be obtained from a likelihood-based longitudinal data analysis model, with responses consisting of all scores (baseline, 90 and 180 days post-randomisation) [14]. The model will include factors representing intervention (SC, MI + SC, RI + SC), time, intervention by time interaction with the restriction of a common baseline mean score across interventions and unstructured variance–covariance among repeated measurements. The model will adjust for the stratification variable (site) used during the randomisation and will be referred to as the unadjusted model. Recruitment site includes Northern Australia, Southern Australia, Norway, the UK, Poland and Germany. The model will include the SC alone group as the reference group.

In sensitivity analysis, variables known to be prognostic of NPI-Q severity (i.e. type of dementia, gender of PwD and CG’s relationship with PwD) will be included in the unadjusted longitudinal data analysis model. This model will be referred to as the adjusted model. The treatment effect estimated from the unadjusted and adjusted models will be the mean difference in NPI-Q severity from baseline to 90 days post-randomisation between the MI plus SC versus SC alone groups.

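### The primary model makes no provision for outcomes being correlated within trainer in the music and reading arms, so the interval for music versus standard care may be too narrow

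*SAP article*

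**What the plan says.** Under Intervention groups, music caregivers are trained by a music therapist ("a qualified music therapist instructed the CG on methods and strategies"). For the reading arm, "The RI involved a 2-h home-based RI instruction session delivered by a qualified practitioner". Caregivers allocated to standard care carry on as usual and have no trainer. Table 1 places training at days 1, 21 and 42 in both trained arms.

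Under Primary outcome, the model contains intervention, time, their interaction with a common baseline mean, and an unstructured covariance among a participant's repeated scores. On site, "The model will adjust for the stratification variable (site) used during the randomisation". The one sensitivity analysis given there adds prognostic covariates. Secondary outcomes are analysed in a similar way. No trainer term or cluster-robust variance appears, and the Sample size section mentions no allowance for clustering.

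The Introduction states that this paper replaces the analysis plans in the registries and the published protocol. It also says that the final plan is to be signed before the allocation code is broken.

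**The concern.** Randomisation is by individual dyad, but delivery in two of the three arms runs through trainers. If some trainers prepare caregivers better than others, dyads with the same trainer resemble each other after baseline. This is a partially nested design: clustering in the trained arms, none in standard care.

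The model has nowhere to put that variation. The site term is the same for all three arms, whereas a trainer effect exists only in a trained arm and only after baseline. It therefore stays in the residual, where it is treated as independent between dyads. At stake is the width of the interval for the primary comparison. The p-value from the same comparison also decides whether music versus reading may be tested at 5% (Multiple testing).

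**Working it through.** **Reproducing the plan's sample size.** The trial was designed "to detect a difference of 3 points in NPI-Q total severity score", with "an equal standard deviation of 7.5 points in the groups". "This assumes 90% power", a two-sided 5% level, and "no correlation between baseline and 12 weeks (conservative) and 20% attrition".

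- Per arm: 2 × (1.960 + 1.282)² × 7.5² / 3² = 131.3, rounded up to 132.
- With 20% attrition: 132 / 0.8 = 165 per arm, and 3 × 165 = 495. Both match the SAP exactly.
- Power at 132 per arm is 90.1%.

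The stated size is thus the size for independent dyads, with no design effect.

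**How likely are shared trainers?** With 165 per arm over six sites, each trained arm averages 165 / 6 = 27.5 dyads per site. Without sharing, each site would need about that many trainers per arm. Sharing is a strong inference, but the SAP gives no trainer count.

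**Effect on music versus standard care.** Let m be the evaluable dyads per trainer and take equal total variance in both arms.

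- Design effect in the trained arm: d = 1 + (m − 1) × ICC; in standard care it is 1.
- True over reported standard error: r = √((d + 1)/2).
- Type I error of the planned test at a zero average effect: 2 × (1 − Φ(1.96 / r)).
- Power of the planned test: Φ((3.25 − 1.96) / r), where 3.25 = 3 / (7.5 × √(2/132)).

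Both m and the ICC are assumptions; neither is in the SAP.

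| m | ICC | d | r | Type I error | Power of planned test |
|---|---|---|---|---|---|
| 8 | 0.01 | 1.07 | 1.02 | 5.4% | 89.7% |
| 8 | 0.05 | 1.35 | 1.08 | 7.1% | 88.3% |
| 11 | 0.02 | 1.20 | 1.05 | 6.2% | 89.1% |
| 11 | 0.05 | 1.50 | 1.12 | 8.0% | 87.6% |
| 16 | 0.01 | 1.15 | 1.04 | 5.9% | 89.3% |
| 16 | 0.05 | 1.75 | 1.17 | 9.5% | 86.4% |

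**Does site adjustment remove it?** This was simulated with two arms of 132, trainers nested in six sites in the trained arm only, site as a fixed effect, one post-baseline score, a zero average effect, and 4,000 runs per cell. The Monte Carlo standard error near 5% is √(0.05 × 0.95 / 4000) = 0.3 percentage points. Rejection rates were:

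| Trainers in the arm | ICC 0 | ICC 0.01 | ICC 0.05 |
|---|---|---|---|
| 24 | 5.0% | 5.2% | 6.3% |
| 12 | 5.0% | 5.7% | 7.6% |
| 6 | 4.9% | 6.2% | 12.7% |

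The rate rises above 5% as the ICC grows and trainers become fewer, although site is in the model.

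**Music versus reading.** If different people trained the two arms, both are clustered and r = √d. Over the same range that is 1.03 to 1.32, with type I error of 5.8% to 13.8%. If the same people trained both arms, a trainer effect common to both would largely cancel.

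**The case against.** The strongest reply is that the inputs are not in the document. It states no caseload and no ICC, and it refers to the protocol for the full description of the interventions. Caregivers deliver the sessions themselves, at least five times a week for 12 weeks, while trainers appear at only three scheduled points. The ICC may well be small. With many trainers and an ICC of 0.01 the effect does not matter in practice. Moreover, if training does nothing for any dyad, trainers cannot differ in effect, and individual randomisation keeps the 5% level. All of this stands, and it makes the point conditional.

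It does not dispose of the point. The SAP reports confidence intervals, and when the effect varies by trainer their coverage falls short whatever the average effect is. The published protocol's analysis plan cannot supply the missing term, because this paper replaces it.

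Three stronger readings are tempting, and the document supports none of them.

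- A reader might infer that the standard errors are too small and the 5% level is lost. That needs shared trainers and an ICC above zero, and neither is stated.
- A reader might infer that music versus reading is worse affected. That needs separate trainers in the two arms, which the SAP does not say.
- A reader might pair the 9.5% type I error with power of 79%. The 79% belongs to a corrected test, Φ(3.25 / 1.17 − 1.96). The planned test keeps about 86% under the same assumptions.

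**Conclusion.** The point holds as an unhandled and conditional risk, not as a demonstrated error. As written, the primary analysis takes dyads to be independent given site, and the site term does not absorb trainer variation confined to the trained arms after baseline.

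If trainers served 8 to 16 dyads each and the ICC is 0.01 to 0.05, the interval for music versus standard care should be 1.02 to 1.17 times as wide as reported, and type I error at a zero average effect is 5.4% to 9.5%. The lower end is negligible. Inflation of type I error requires an average effect of zero with trainers who differ; with no training effect on any dyad there is none. Music versus reading would be affected more only if the trainers differed between those arms. A sensitivity analysis is the proportionate response; the primary analysis need not be replaced.

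**What to change.** Before unblinding, add to the Primary outcome section a prespecified sensitivity analysis:

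- Fit the primary model with a random trainer effect on post-baseline scores in the music and reading arms only, leaving standard-care dyads unclustered, and use a small-sample degrees-of-freedom correction.
- If it does not converge, use standard errors clustered on trainer, with each standard-care dyad as its own cluster. A small-sample correction is needed here too, because trainers may be few: at 16 dyads per trainer, 132 / 16 is about 8 per arm.
- Report the number of trainers, the dyads per trainer, whether trainers overlapped between arms, the trainer ICC, and both confidence intervals.
- State in advance that the primary result will be described as not robust to trainer clustering if the sensitivity interval includes zero and the primary interval does not.

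The cost is merging trainer identity into the analysis data and fitting one extra model. The interval may be slightly wider, and the ICC will be imprecise if trainers are few.

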### Eligibility

Dyads were eligible to participate in the study if they were co-habiting in their own homes (i.e. not supported residential care) and the CG was providing care for the PwD. In addition, one member of the dyad had to have a dementia diagnosis (e.g. Alzheimer’s disease, frontotemporal dementia, vascular dementia, Lewy body disease, mixed dementia) and have a score of at least 6 on the NPI-Q. Dyads were not eligible to participate if either or both the CG and PwD had a significant hearing impairment that was not resolved with a hearing aid device as this could limit their capacity to enjoy musical experiences. In addition, participants with no internet access were also excluded from the study. Full recruitment details can be found in the published study protocol [9].

### Randomisation

Dyads were randomly allocated to one of the three intervention groups with a 1:1:1 allocation using a computer-generated schedule of randomly permuted blocks, stratified by site (Queensland [Australia], Victoria [Australia], Germany, Norway, Poland and the UK) to achieve a balance between the arms within each stratum. The list was created by an independent statistician and uploaded to the randomisation module of the REDCap (Research Electronic Data Capture) trial database hosted at the University of Melbourne [10]. The study aimed to have equal numbers of participants within each country. However, due to recruitment challenges at some sites, other sites increased their recruitment target to maximise recruitment. Participating dyads could not be fully blinded due to the active nature of the interventions. The assessors and biostatisticians were blinded to the allocation during the conduct of the trial and will not be unblinded until the database is ready for breaking of the code.

### Sample size

The trial was designed to recruit a total of 495 dyads (165 per arm) to detect a difference of 3 points in NPI-Q total severity score between the MI plus SC and SC alone at 90 days post-randomisation. This assumes 90% power, a two-tailed significance level of 5%, an equal standard deviation of 7.5 points in the groups, no correlation between baseline and 12 weeks (conservative) and 20% attrition. A 3-point change from baseline in NPI-Q total severity score is considered a clinically meaningful difference [11]. No interim analyses to stop the trial early were planned, and no interim analysis was conducted.

### Timing of outcome assessments

The expected visit dates in Table 1 describe the timing of all outcome measures.

**Table 1 Tab1:** Schedule of enrolment, interventions and assessments

	**Enrolment**	**Allocation**	**Intervention**			**Post-Intervention**	**Follow-up**
**Time point**	***Day − 1***		***Day 1***	***Day 21***	***Day 42***	***Day 90***	***Day 180***
**Enrolment:**							
**Eligibility screen**	X						
**Informed consent (or assent)**	X						
**Dyad: allocation**		X					
**Interventions:**							
***Music intervention training***			X	X	X		
***Reading intervention training***			X	X	X		
**Assessments:**							
**Person with dementia *****sociodemographic information***	X						
**MMSE***** (self)***	X					X	
**Dementia diagnosis***** (proxy)***	X						
**NPI-Q***** (proxy)***	X					X	X
**MADRS *****(proxy)***	X					X	X
**QoL-AD *****(self and proxy)***	X					X	X
**EQ-5D-5L *****(self and proxy)***	X					X	X
**Adverse events; death, hospitalisation, death of CG**			X	X	X	X	X
**Caregiver** ***sociodemographic information***	X						
**PHQ-9**	X					X	X
**RS-14**	X					X	X
**SSCQ**	X					X	X
**QCPR**	X					X	X
**AQoL-6D**	X					X	X
**EQ-5D-5L *****(self)***	X					X	X
**RUD**	X					X	X
**Post-training questionnaires**			X	X	X		
**Interviews**						X	
**Diary (5 × weekly diary entries for MI and RI)**			X	X	X	X	
**Adverse events: death, hospitalisation**			X	X	X	X	X

Brackets denote who the measure represents (i.e. caregiver (CG), person with dementia (PwD) or dyad), although in some cases the CG provides a proxy measure for the PwD

The EQ-5D-5L and RUD are used in the cost-effectiveness analyses and their analyses are not detailed in the statistical analysis plan

*MMSE* Mini-Mental State Examination Score, *NPI-Q* Neuropsychiatric Inventory Questionnaire, *MADRS* Montgomery-Asberg Depression Rating Scale, *QoL-AD* Quality of Life-Alzheimer’s Disease, *EQ-5D-5L* The EuroQol instrument, *PHQ-9* Patient Health Questionnaire, *RS* Resilience Scale, *SSCQ* Short Sense of Competence Questionnaire, *QCPR* Quality of Caregiver-Patient Relationship, *AQoL-6D* Assessment of Quality of Life-6D instrument, *RUD* Resource Utilisation in Dementia, *MI* Music intervention, *RI* Reading intervention

### Statistical principles

The analysis will be conducted by biostatisticians from the Methods and Implementation Support for Clinical and Health (MISCH) Research Hub (University of Melbourne, Australia). After all study data are available and have been cleaned, a blinded review meeting will be held prior to database lock. The final statistical analysis plan will be signed off before breaking the blind. The analysis of the primary outcome will be independently checked by a senior biostatistician at MISCH and any discrepancies between the two analyses will be discussed and resolved by consensus. All statistical tests will be performed in Stata/SE version 16.1 (Stata Corporation, College Station, TX, USA), and confidence intervals (CIs) reported, at the two-sided 5% level of significance unless stated otherwise.

### Multiple testing

There are a total of three treatment comparisons: (1) MI plus SC vs SC only (2) RI plus SC vs SC only and (3) MI plus SC vs RI plus SC. The comparison of MI plus SC vs SC only and RI plus SC vs SC only will occur at the 5% level of significance. The comparison of MI plus SC vs SC only is the primary comparison. A hierarchical fixed sequence testing procedure will allow for comparison of the primary outcome (NPI-Q severity total score) between MI and RI at 90 days at the 5% significance level if there is strong evidence (*p* < 0.05) of a treatment effect for this outcome comparing MI plus SC and SC only at 90 days.

Secondary outcomes were not powered for. Therefore, no multiplicity adjustment for the analysis of the secondary outcomes will be adopted. Instead, all effect sizes, CIs and *p*-values will be reported to let readers use their own judgement about the relative weight of the conclusions on the effect of the interventions on the secondary outcomes. This approach aligns with the usage of *p*-values favoured by the American Statistical Association [12]. This approach will also be used for exploratory subgroup analyses.

